### 2.1. Study Setting

This study will be conducted in the different leading hospitals of the Valencian Community, in the Pneumology, Endocrinology, and Allergology units. This study is a quasi-experimental design with repeated measures. Each participant receiving the intervention (experimental condition)will also act as their control grorup. Therefore, the physical and psychological diagnostic measures will be collected from all of participants in an initial assessment (T1) and, secondly, six months after the initial assessment and right before starting the treatment programme (T2). At these two assessment points (T1 and T2), all participants (patients and family members) will be assessed (T2). The treatment lasted for five sessions for adolescents, with one individual session per month and two sessions for family caregivers (month 4 and month 5). The treatment programme will begin in the maximum expected time of 15 days from the second pre-treatment assessment (T2), with an estimated duration of 5 months. After the end of the treatment sessions for the patient and their family members, a new diagnostic test (T3) will be conducted (across all variables), within an expected maximum time of 15 days until the end of the treatment, to assess the post-treatment change. Thus, the estimated time between T1 and T2 is the same as that between T2 and T3, which is six months. The programme of registration, interventions, and evaluations (SPIRIT Programme) is shown in Table 1 and Table S1. 

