### 2.2. Patient and Public Involvement

Participants will be recruited when receiving hospital care. Inclusion criteria will be (1) participants must be adolescents from 12 to 16 years of age, with (2) a diagnosis of CD (endocrinologic, such as DM1, or pneumo allergic diseases) within the last 6 months. Exclusion criteria will be (1) the presentation of a psychiatric disorder prior to the disease; (2) epilepsy, infantile cerebral palsy, or brain tumours; and (3) not understanding the Spanish language. All the parents of recruited adolescents will be offered the opportunity to participate in shorter sessions to promote self-care and family bonding. The parent training will be conducted in two 2-h sessions. The trainers will be psychologists specialised in health psychology who, prior to the start of the program, will receive hours of training in the 10Vida program.

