### 2.7. Recruitment

Endocrinologists, pulmonologists, and allergists will be responsible for recruitment, which will take place in the hospital during routine patient visits. Participants will be asked to complete a battery of questionnaires on their psychological and physical health statuses in a single session. The design of this intervention consists of patients and caregivers who receive the treatment program, who will act as their own control group; then, after six months, the 10Vida intervention will be initiated. The outcome measures will be collected by the medical and psychological specialists.

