#### Statistical Methods

Independent-samples *t*-tests and chi-square tests were performed to determine pre-intervention differences between participants with and without missing values in the variables studied. In addition, chi-square tests were undertaken to compare the number of people who dropped out of the research in the experimental group with those who dropped out in the control group, and it was found that they did not differ significantly.

Before testing the change models, descriptive analyses, Pearson correlations, and multivariate and univariate variance analyses (MANOVA and ANOVA) were performed with the pre-intervention scores of the participants in the experimental and control groups to identify possible differences in the baseline. Likewise, multivariate and univariate covariance analyses (MANCOVA and ANCOVA) were performed to identify changes in the post-intervention scores (short-term effect), while controlling for the pre-intervention scores (covariate). In addition, the effect size (Cohen’s *d*) of each variable was calculated to estimate the magnitude of the differences between the experimental and control groups. These analyses were performed with the statistical package SPSS V.26.

Multiple hierarchical regression analyses were conducted to examine the added predictive value of the experimental condition to explain the effectiveness of the intervention programme [46]. Firstly, the pre-intervention assessment score (control variable) was introduced, and then the experimental condition (1 = experimental intervention group, 0 = control group) was introduced as an independent variable. The dependent variable was the change variable between pre- and post-interventions, as well as between pre-intervention and the follow-up of the emotional and well-being variables. In this sense, the statistically significant change of the determination coefficient in model 2 (predictor: experimental condition, controlling for the pre-intervention score) is interpreted as an added predictive value. The significant prediction of the experimental condition, controlling for the pre-intervention score, leads us to attribute the significant change to the intervention. All data shall be entered electronically. Participant files will be recorded securely and will be stored for a period of 10 years after the end of the study.

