Despite the strengths and potentials of the study, especially its multicentre scope and its ability to adapt to different pathologies suffered by adolescents, which will allow for the comparison of results between groups, this study has certain limitations. The fact that the control group is a waiting list control group may mean that the results are not directly attributable to the intervention programme. In addition, the samples we intend to access are difficult to access, and the study will not compensate participants financially, so the number of participants may be small. Nevertheless, the team will try to encourage the motivation of adolescents and their families to participate, and will widely disseminate the programme to try to reach as many participants as possible.

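### The rule that credits a significant, pre-score-adjusted condition term to the intervention is invalid here, because condition is fully confounded with period and time since diagnosis

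*Protocol article*

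**What the plan says.** Section 2.1 of the protocol article describes the design: "This study is a quasi-experimental design with repeated measures". Section 2.7 says that participants are those "who will act as their own control group; then, after six months, the 10Vida intervention will be initiated". Table 1 marks allocation as not applicable, so there is no separate control group, and for every participant the untreated period comes first. Section 2.1 adds: "Thus, the estimated time between T1 and T2 is the same as that between T2 and T3, which is six months". Section 2.2 requires "a diagnosis of CD (endocrinologic, such as DM1, or pneumo allergic diseases) within the last 6 months".

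The Statistical Methods section nevertheless describes a two-group regression. The pre-intervention score is entered first, and then "the experimental condition (1 = experimental intervention group, 0 = control group) was introduced as an independent variable". The outcome is a change score: "The dependent variable was the change variable between pre- and post-interventions". The section closes with the rule at issue: "The significant prediction of the experimental condition, controlling for the pre-intervention score, leads us to attribute the significant change to the intervention".

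The Discussion takes the opposite position. It says that the type of control group "may mean that the results are not directly attributable to the intervention programme".

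**The concern.** The rule turns a p-value into a causal claim. That needs the 0 and 1 conditions to differ, on average, only in the programme once the pre-score is held fixed. Here they also differ in calendar period and in time since diagnosis, for every participant and in the same direction.

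The primary patient outcomes (emotional adjustment, emotional competence, perceived illness threat, self-esteem) could plausibly move by themselves in the first year and a half after a diagnosis. If they do, the condition term picks up that movement. Adjusting for the pre-score does not remove it, and can produce a non-zero term even when the natural change is identical in the two periods.

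At stake is the study's second aim, the effectiveness conclusion. Under the rule as written, an ineffective programme could be declared effective, or a useful one could look ineffective or harmful.

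**Working it through.** **Where the visits fall.** Entry is at most 6 months after diagnosis and the visits are about 6 months apart. So T1 lies at 0–6, T2 at 6–12 and T3 at 12–18 months after diagnosis. The untreated period ends at 6–12 months and the treated period at 12–18 months. Nobody is observed untreated after month 12, and nobody is observed after the programme before month 12. The data hold no contrast that separates programme from elapsed time.

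**Inputs.** The main-study size, about 200, is from section 2.6. The article gives no alpha, effect size, SD or correlation, so the following are assumptions:
- two-sided 0.05;
- SD 1 at each visit;
- equal between-visit correlation rho of 0.5 to 0.7;
- natural improvement d1 over T1–T2 and d2 over T2–T3 (higher = better);
- programme effect exactly zero.

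The article does not say how the 0 and 1 rows are formed from one cohort. I assume two rows per person: condition 0 with pre = T1 and change = T2−T1, and condition 1 with pre = T2 and change = T3−T2. I found no other layout that yields a 0 group from this cohort.

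**Expected coefficient.**
- Difference in mean change, 1 minus 0: d2 − d1.
- Difference in mean pre-score, 1 minus 0: d1.
- Slope of change on pre-score: rho − 1.
- Condition coefficient = (d2 − d1) − (rho − 1)·d1 = **d2 − rho·d1**.

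Under no programme effect this is zero only if d2 = rho·d1.

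**Equal natural improvement, d1 = d2 = 0.25 SD, n = 200.** The coefficient is (1 − rho)·0.25. Rejection rates are simulated; repeat runs differ by a point or two.

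| rho | Spurious effect (SD) | Rejection, rows treated as independent | Rejection, errors clustered by person |
|---|---|---|---|
| 0.5 | 0.125 | 32% | 27% |
| 0.6 | 0.100 | 28% | 22% |
| 0.7 | 0.075 | 21% | 14% |

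Two causes are mixed in the third column. With no natural change at all, the stacked model already rejects about 7–9%, because each person's two rows are treated as independent. The clustered column removes that part. At 0.10 SD per period and rho 0.6 the stacked model rejects about 10%, most of which comes from the ignored dependence and not from adaptation.

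**Other natural courses.**
- Slowing, d1 = 0.5, d2 = 0.25: the coefficient is 0.25 − 0.5·0.5 = 0 at rho 0.5, and 0.25 − 0.6·0.5 = −0.05 at rho 0.6. At rho 0.6 the favourable false-positive rate is about 1%.
- Strong slowing, d1 = 0.5, d2 = 0.1, rho 0.7: 0.1 − 0.35 = −0.25. With n = 200 about 89% of runs are significant, all against the programme.
- Worsening by 0.25 SD per period, rho 0.6: −0.25 + 0.15 = −0.10, against the programme.
- Accelerating, d1 = 0.2, d2 = 0.3, n = 200: about 60–62% significant in the programme's favour (rho 0.7 and 0.5).

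**The unadjusted contrast (T3−T2) − (T2−T1).** Its expectation is d2 − d1, so a linear natural trend cancels and rejection stays near 5%. With d1 = 0.5, d2 = 0.25 and rho 0.6 the expectation is −0.25. The standard error is √(6·(1−0.6)/200) = √0.012 = 0.110, so the ratio is about −2.3. An ineffective programme is then rejected, in the harmful direction, in about 62% of runs.

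**The case against.** The strongest reply is that the bias has no fixed direction. A reader might infer that natural adaptation by itself always yields a favourable result, or that adjusting for the pre-score always makes matters worse. The documents support neither. They give no natural-course figures, and slowing adaptation after a recent diagnosis is at least as plausible as a constant rate. In the slowing case above, the pre-score-adjusted model is less biased (−0.05) than the unadjusted contrast (−0.25). This part of the reply stands. It limits the size and sign of the error but does not rescue the rule, whose validity would then depend on an unknown trend shape.

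Second, the stacked layout is a reading of an unclear text, and part of the inflation comes from dependence between rows. Both points stand and are shown above. The confounding itself depends on neither.

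Third, the article declares a quasi-experimental design, includes an untreated period of about equal length, records time of diagnosis (section 2.8), and concedes the attribution problem in the Discussion. That is fair as disclosure. But a limitation in the Discussion does not cancel an operative rule in the Methods, and the two now contradict each other.

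Finally, a reader might infer that the own-control design is itself an error and that the study must be randomised. It is a declared design choice with known limits. What is wrong is the conclusion that the rule draws from it.

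**Conclusion.** The attribution rule is wrong as written. Condition is the same variable as period and, within a person, moves in step with time since diagnosis. No significance test on that term can identify a programme effect, and the Discussion concedes the point. This conclusion rests only on the stated design.

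The size rests on assumptions: stacked rows, equal correlations, and 0.25 SD natural improvement per period. For 200 participants and rho 0.7 to 0.5 these give a spurious effect of 0.075 to 0.125 SD and false-positive rates of about 21–32%, or about 14–27% with clustered errors. Natural adaptation can produce a significant result; it need not, and enough slowing or any steady worsening removes or reverses the bias.

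**What to change.** Minimum correction:

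1. Replace the attribution sentence with wording that describes the change as associated with the intervention period, in line with the Discussion.
2. Replace the independent-group 0/1 regression with a within-person model of T1, T2 and T3 that accounts for repeated rows, uses actual visit dates (the equal six-month intervals are only estimates), and reports (T3−T2) − (T2−T1) with its confidence interval.
3. State that this contrast removes only a linear natural trend and so does not support causal attribution either. Time since diagnosis may be added, but it separates programme from elapsed time only under an assumed trend shape, which should be named.

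The cost is a weaker stated conclusion and a little more analysis work, with no extra patients or visits.

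Optional redesign, not part of the minimum: in the main study, which the article schedules for a later start, randomise families to an immediate or a six-month-delayed start. The comparison at T2 adjusted for T1 would then permit causal attribution. At rho 0.6 and 80% power the minimum detectable effect would be 2.80·√(2·(1−0.36)/100) = 0.32 SD with 100 per arm, against 2.80·√(6·0.4/200) = 0.31 SD for the own-control contrast with 200. It would need a protocol and registry amendment and would change how therapist workload is spread.

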### 2.9. Ethics and Dissemination

Each participant will receive information about the aim and procedures of the study and will provide written consent for participation. Consent and assent will be obtained by the medical specialist. The data will be confidential and anonymised, and will be used solely for the objectives of the study (27 April 2016 Data Protection Act (GDPR)). Numerical codes will link each participant’s identification information. The data collected will be stored in a locker in the place of work of the principal investigator, and electronic data will be protected by password on the university network computer. Any protocol amendments will be registered at ClinicalTrials.gov (NCT04476433).

## 3. Discussion

The present study aims to design a strengths-based intervention programme for adolescents with a CD and their families. The expected results of this study could incorporate improvements in routine clinical practice. This programme will provide an effective tool to improve physical and emotional health. The design of this intervention programme has been based on previous psychological interventions [26,27,30,31], encompassing different components explored in the different research studies. However, one advantage is that it incorporates the caregiver in the programme, and it is carried out on an individual basis.

The second objective of the study is to assess the efficacy of the programme on indicators of physical and emotional adjustment immediately after the programme. We expect that adolescents will improve their personal strengths and, therefore, there will be an increase in their emotional skills, and their well-being, as well as an improvement in their social and family relationships and their quality of life, and a decrease in psychopathology. Similarly, we expect some medical indicators (glycaemic control, densiometry, analytical controls, spirometry, plethysmography, or the prick test) to improve or remain stable, as other programmes targeting adolescents with CDs have shown [30,31].

At the same time, including family caregivers in the intervention can provide us with an improvement in emotional health indicators and their personal protective factors, which can directly influence the physical and emotional well-being of their children [26].

The results after the implementation are expected to show the success of personal strengths enhancement, underlining the importance of family system-based interventions to enhance personal skills and treatment adherence in adolescents with CD [26,46]. Therefore, our intervention programme will consider primary caregivers in its sessions, dedicating two of the seven sessions to the management of the CD in the family setting. We believe that this intervention may be more effective than interventions specifically targeting adolescents, without taking their families into account [26].

The preliminary findings obtained from the current pilot study on adolescents with type 1 diabetes mellitus and their caregivers suggest that the 10Vida program provides an opportunity to enhance the physical and psychological adjustment of adolescents with a chronic disease, as well as their families.

Despite the strengths and potentials of the study, especially its multicentre scope and its ability to adapt to different pathologies suffered by adolescents, which will allow for the comparison of results between groups, this study has certain limitations. The fact that the control group is a waiting list control group may mean that the results are not directly attributable to the intervention programme. In addition, the samples we intend to access are difficult to access, and the study will not compensate participants financially, so the number of participants may be small. Nevertheless, the team will try to encourage the motivation of adolescents and their families to participate, and will widely disseminate the programme to try to reach as many participants as possible.

## 4. Conclusions

To our knowledge, this is the first programme specifically aimed at increasing the personal strengths of adolescents with endocrine, respiratory, or allergic CD, which also considers their families. Although an intervention protocol addressing emotional skills in adolescents with type 1 diabetes mellitus exists [49], no results are known to date. In addition, most intervention programmes are aimed at reducing psychopathology, but do not assess the enhancement of the protective factors in the family. Enhancing personal strengths in the families of adolescents with CDs may help them to better adapt to the disease and, therefore, manage it better. This may improve the course and development of CDs and prevent future medical complications.

## 5. Patents

This intervention protocol is registered as intellectual property at the Universitat de València, under the registration number of UV-MET-202131R (Registered on 24 May 2021)

## Figures and Tables

**Figure 1 ijerph-19-03162-f001:**
[figure not shown]
Presentation of the 10Vida programme and its areas.

**Table 1 ijerph-19-03162-t001:** Time schedule for study period with phases and assessments.

	Enrolment	Allocation			
TIMEPOINT **	*T1 (Own control group)*	0	*Pre test (t_2_)*	*Intervention*	*Post test (t_3_)*
**ENROLMENT**					
Eligibility screen	X				
Informed consent	X				
Allocation		Not applicable			
**INTERVENTIONS**					
*“10Vida”* intervention (experimental group)			X	X	X
**ASSESSMENTS**					
**Primary outcomes of patients**					
Sociodemographic data	X				
Emotional adjustment	X		X		X
Emotional competencies	X		X		X
Perceived illness threat	X		X		X
Self-esteem	X		X		X
**Secondary variables of patients**					
Adaptation to chronic disease	X		X		X
Parental parenting style	X		X		X
Psychological well-being	X		X		X
Physical or clinical measure (i.e., Hba1c)	X		X		X
Satisfaction with programme					X
**ASSESSMENTS**					
**Primary outcomes of caregivers**					
Sociodemographic data	X		X		X
Emotional adjustment	X		X		X
Burden or stress	X		X		X
**Secondary outcomes of caregivers**					
Resilience	X		X		X
Family functioning	X		X		X
Satisfaction with programme	X		X		X

**Table 2 ijerph-19-03162-t002:** 10Vida program summary. Sessions and objectives.

10VIDA PROGRAM		
Sessions with Patients (5)		
Name of Session	Theme	Aims
S1. Mis creencias	Adjustment to illness	Assess, recognise, and value beliefs, concerns, or fears related to the disease
S2. Una mirada a mi interior	Self-esteem/self-concept	To develop behavioural patterns that facilitate an adequate self-image and identity, without the stigmas of illness
S3. Desde la serenidad	Coping with fear	To learn to identify, attend to, and manage the anxious symptomatology associated with the life situations that a chronic disease in adolescence may entail. To favour a serene and positive attitude, knowing their own fears
S4. Las emociones: Mis amigas	Emotional self-regulation	Encourage a coping and resilient attitude to facilitate the acquisition of appropriate habits and behaviours. To promote positive emotions that can cushion the daily situations with the disease
S5. Una mirada al exterior	Social area	To reflect on the importance of friendships at this age, and that they are sources of support in the face of illness and treatment
S6. Me cuidas, te cuidas	Caregiver needs	Know and address the psychological and emotional needs of primary caregivers by providing them with strategies. Intervene in the beliefs and concerns regarding the disease, their child, themselves, or the family
S7. Unidos, sumamos	The family system	Emphasise the role of parents in coping with their child’s illness, reducing stress, and encouraging acceptance. Encourage a democratic parenting style

**Table 3 ijerph-19-03162-t003:** Content of 10Vida activities.

Session	Theme/Variable	Activity	Activity Objectives
S1. Mis creencias	Adjustment to illness	A1.1. Well_lived chronic disease	Provide the adolescent a leading role and create a safe space for them to express themselves and grow emotionally Recognise the main concerns that generate fear and the place of their illness within them Express and recognise feelings, beliefs, and thoughts about their illness
		A1.2. Deal	To provide tools for decision making in their life beyond the disease Respond to their emotions and thoughts to guide them towards achieving their goals and coping with their fears
S2. Una mirada a mi interior	Self-esteem/self-concept	A2.1. I am and not my disease	Work on the importance of self-reflection Encourage learning to look at and discover oneself with serenity and affection Define self-esteem and self-concept Reflect on the role of the disease in one’s self-image
		A.2.2. Because I’m worth it	Self-awareness and self-discovery: strengths, weaknesses, and needs
		A2.3. I spoke nicely	Reflect on the importance of words and their effect on thoughts and action Work on positive language and the effect of negative thoughts
S3. Desde la serenidad	Coping with fear	A.3.1. I listen to my signs	Through an explanation supported by drawings, learn the difference between fear and anxiety Understand how fear/anxiety works Learn how to detect and identify signs of fear/anxiety in your body
		A.3.2. My monster and I	Give name, form, “life” to the “monster” to have more control and stop fearing it Training of self-regulation resources
		A.3.3. The eye outwards	Explain the mindfulness-based technique: mindfulness in everyday life Learn to discover and be amazed by their surroundings and what they may not have noticed
S4. Las emociones: Mis amigas	Emotional self-regulation	A.4.1. Emotions, my Friends	Define the concept of emotions, their functions, and their meanings To facilitate personal emotional identification and expression To train in emotional skills
		A.4.2. Emociometer	Continue working with emotions and their functions Increase emotional vocabulary Training in emotional skills
		A.4.3 D&D	Discover effective strategies for expressing emotions
S5. Una mirada al exterior	Social area	A.5.1. I’m not alone.	Understanding the influence of others in our lives To observe how the disease has affected relationships and social situations
		A.5.2. Social superhero	Demonstrate the main social skills for their stage of development and describe the skills with them Social skills training
		A.5.3. Colour glasses	Learning to perceive the world through a more positive language
S6. Me cuidas, te cuidas	Caregiver needs	A.6.1. It is in my	Ask parents about the influence of their children’s disease on their own lives Provide a space and a place for them to express their fears, worries, frustrations, etc.
		A.6.2. Welcome adolescence	Provide a perspective of adolescence as both a challenge and an opportunity rather than a risk Explore the changes in the adolescent developmental process
		A.6.3. Because I also exist	Working on the importance of self-care
S7. Unidos, sumamos	The family system	A.7.1. Yes to love	Reminding parents of the importance of the bond of attachment with their children To give specific hints on how to show affection at this age and according to their individual needs
		A.7.2. I control	Explain to parents the need to control their children at the adolescent stage Working on learning styles
		A.7.3. Living without whatsapp	Provide information on the quality and quantity of communication with an adolescent Provide keys to more positive communication, favouring warmth and minimising conflicts

